## Abstract

**Background:**

Limited research has examined the direct effectiveness of *Helicobacter pylori* eradication (HPE) on the remnant stomach neoplasms after curative gastrectomy. This study aims to assess whether HPE could prevent the development of gastric neoplasms in the remnant stomach after curative gastrectomy through a double-blinded, randomized controlled trial.

**Methods:**

After curative gastrectomy, patients with HP infection and pathologically proven stage 1 tumors will be enrolled and randomly assigned to eradication (n = 492) and placebo (n = 492) groups. Patients in the eradication arm will be given the eradication regimen, which will comprise 40 mg of esomeprazole, 1 g of amoxicillin, and 500 mg of clarithromycin twice a day for 14 days. The primary endpoint is the development of gastric neoplasms, including adenoma or adenocarcinoma. The secondary endpoints are the 10-year overall survival, improvement rates of gastric glandular atrophy and/or intestinal metaplasia, and incidence of new-onset hyperplastic polyps among the groups.

**Significance:**

This research will be the first randomized controlled clinical study in which a thorough long-term follow-up will be needed to evaluate the effectiveness of HPE for remnant stomach neoplasms after curative gastrectomy. Its results will serve as a basis for developing future strategies in the management of patients with HP infection who undergo curative gastrectomy.

**Trial registration:**

https://cris.nih.go.kr/ KCT0008855. October 10, 2023.

## Introduction

The causal relationship between *Helicobacter pylori* (HP) infection and the development of gastric cancer is well established. Previous studies reported the preventive effect of HP eradication (HPE) on the occurrence of gastric cancer [1–4]. Furthermore, HPE therapy has successfully decreased the risk of recurrent gastric neoplasms after endoscopic resection. Specifically, compared with untreated patients, patients treated with an eradication regimen experience 35%–50% reduction in the incidence of metachronous gastric adenoma and/or adenocarcinoma after endoscopic resection of the index neoplasm [5,6].

In contrast to the widely studied remarkable reduction in the incidence of gastric neoplasms after endoscopic resection but preserving entire stomach, the effect of HPE on the condition of the remaining stomach after distal or subtotal gastrectomy has been rarely investigated [7–9]. Theoretically, after surgery, the acidic condition within the stomach is inevitably changed because of alkaline reflux from small intestine, markedly reduced parietal cell volume, and denervation of vagus nerve. Based on these postoperative changes, some recent studies reported even spontaneous remission of HP in the remained stomach [10–14]. On the contrary, a previous study showed the potential role of eradication therapy after distal gastrectomy, which can improve precancerous lesions, such as glandular atrophy or intestinal metaplasia, in the remnant stomach [7]. Another study reported that the HPE rate of patients who underwent subtotal gastrectomy is similar to that of patients who did not undergo surgery, and the atrophy and intestinal metaplasia scores were significantly lower in the successful eradication group than in the other group [9]. On the basis of these findings, both studies recommended HPE after subtotal gastrectomy. In addition, a large retrospective study demonstrated remarkable prognostic benefits, namely, overall and gastric cancer-specific survival, in patients who received HPE therapy compared with those who did not have the same treatment [8]. However, studies have yet to elucidate whether HPE can effectively and directly prevent the occurrence of remnant stomach neoplasms after curative gastrectomy to provide high-level evidence. Consequently, in the patient group who receive surgery, the necessity of HPE was not proven and included in the current treatment guideline. To fill this gap, we aim to determine whether HPE can reduce the development of gastric neoplasms occurring in the remnant stomach after curative gastrectomy through a double-blinded, randomized controlled trial (RCT).

## Materials and methods

This clinical trial is a single-center investigator-initiated, RCT that aims to analyse the effect of HPE on remnant stomach neoplasms after curative gastrectomy. The study will be conducted at Asan Medical Center, Seoul. Korea. It is scheduled to begin on June 27, 2024, and is expected to conclude on December 31, 2038. Participant recruitment will be completed by December 31, 2028. The final patient follow-up and data collection are expected to conclude by December 31, 2038. The study results are anticipated to be available by June 30, 2039. The status of this trial is now participant recruitment. Fig 1 summarizes the schedule of this trial.

**Fig 1 pone.0320903.g001:**
[figure not shown]
Schedule of the study.

### Objectives

Primary objective. This study aims to evaluate the effect of HPE on the occurrence of gastric neoplasms, including adenoma or adenocarcinoma, in the remnant stomach of patients who undergo curative gastrectomy for gastric cancer. The follow-up period for assessing these outcomes will be 10 years.Secondary objectives. This study aims to examine the following: 1) 10-year overall survival, 2) improvement rates of gastric glandular atrophy and/or intestinal metaplasia, and 3) incidence of new-onset hyperplastic polyps among the groups.

### Study protocol

1Baseline evaluation.1)All patients will undergo a history taking to determine whether they have previously received HPE therapy. The following tests will be performed to verify whether the patient had current HP infection prior to surgery: urea breath test, rapid urease test (RUT), and histological evaluation with Giemsa staining or immunohistochemistry (IHC).

HP infection will be diagnosed when any of the three studies showed positive results.All patients will be asked to take a 100 mg tablet of ^13^C-urea (UBiTkit; Otsuka Pharmaceutical Co., Ltd., Tokyo, Japan) with 100 mL of water after 4 h of fasting. Two breath samples will be collected before and 20 min after the patients swallow the tablet. A cut-off value of ^13^CO_2_ < 2.5% will be considered HP negative [15].

2)Gastric glandular atrophy and intestinal metaplasia, which are known precancerous conditions, will be evaluated in biopsy specimens obtained from the gastric antrum, body, and fundus by using the updated Sydney system. Serum pepsinogen I and II concentrations and pepsinogen I/II ratio will also be assessed.

Surgery. The patients will be subjected to curative gastrectomy with D1+ or D2 lymph node dissection based on clinical or surgical staging. Surgical treatment will be performed according to the gastric cancer treatment guidelines of Korea and Japan [16,17]. Reconstructive procedures will be selected depending on the surgeon’s preference.Patient enrollment. At the first outpatient clinic visit after surgery (3–4 weeks after surgery), consecutive patients with HP infection and pathologically proven stage 1 tumors will be enrolled in accordance with the following criteria for patient eligibility. Fig 2 presents a schematic diagram of the study protocol.The pathological stage will be determined on the basis of the results of the histopathological examination of the resected specimen. The depths of invasion (T stage) and lymph node involvement (N stage) of tumor cells will be evaluated according to the 8th edition of the International Union Against Cancer/American Joint Committee on Cancer Staging manual.Surgical curability is determined when pathological findings confirm the absence of residual tumor and an R0 resection has been achieved during the procedure.

**Fig 2 pone.0320903.g002:**
[figure not shown]
Schematic diagram of the study protocol.

#### Eligibility.

The following patient inclusion and exclusion criteria will be considered:

#### Inclusion criteria.

Patients will be considered eligible if they are adult patients (a) aged 19–70 years, (b) who are diagnosed with HP infection (c) diagnosed with pathologic stage 1 gastric cancer, (d) subjected to distal gastrectomy for cancer located in the lower half of the stomach (pylorus, antrum, and lower body), and (e) subjected to proximal gastrectomy for cancer located in the upper half of the stomach (fundus, cardia, upper body, and mid body) requiring either upfront curative gastrectomy or additional surgery after noncurative endoscopic resection.

#### Exclusion criteria.

Patients will be excluded if they have the following:

1)history of HPE2)history of previous gastrectomy3)history of any malignancy within the last 10 years4)Patient who previously underwent endoscopic treatment on the section that will become the remnant stomach5)patients who require adjuvant/neoadjuvant chemotherapy6)history of allergy or serious adverse events to prescribed medication, including amoxicillin and clarithromycin7)presence of severe comorbidities (e.g., cardiac, hepatic, or renal insufficiency) or coagulopathy8)pregnant or lactating women9)presence of a psychiatric disorder that might preclude compliance 10)patients who could not provide informed consent 11)Borrmann type 4 tumors (linitis plastica) on tumor classification 12)proximal resection margin shorter than 3 cm in advanced gastric cancer 13)withdrawn consent4Randomization.

Patients will be randomly assigned to one of the two arms in a 1:1 fashion. After the stratification of gastrointestinal reconstruction (distal gastrectomy with Billroth 1 [gastroduodenostomy] or Billroth 2 [gastrojejunostomy] or Roux-en-Y gastrojejunostomy and proximal gastrectomy with double tract reconstruction) methods, centralised stratified block randomization will be used to randomly assign the patients to the two groups.

We have performed a stratified block randomization method using a permuted block design. Stratified randomization is achieved by generating a separate block for each stratification factors, and patients are assigned to the appropriate block of stratification factors. After all patients have been identified and assigned into blocks, simple randomization occurs within each block to assign patients to one of the groups. Because the clinical trial is ongoing, we cannot provide the block size used.

An interactive web-response system will be used for randomization. The patients will be assigned to each treatment group according to the allocation codes provided by the random assignment program, and seeds will be assigned to the random assignment codes to enable reproducibility.

Double-blinding will be applied to patients and investigators. Regarding drug administration, the site investigators will check the assigned randomized drug number in order of the serial number, prepare the drug, and administer it to the patients. All the data collected from each individual patient and from the individual blinding codes will not be broken for preplanned data analysis until the database is locked.

Details on treatment.Group A (Eradication arm) Patients in the eradication arm will receive the eradication regimen consisting of 40 mg of esomeprazole (a proton pump inhibitor), 1 g of amoxicillin, and 500 mg of clarithromycin twice a day for 14 days.Group B (Placebo arm) Patients in the placebo arm will receive placebo tablets that are identical in appearance to the active drugs used in the eradication regimen. This ensures that both the patients and the investigators remain blinded to the treatment allocation.

All Patients will be provided with medication logs to record the administration of either the active drugs or placebos. These logs will be reviewed during follow-up visits.

Follow-up strategy.In accordance with the Korean gastric cancer treatment guidelines, patients will be followed up with physical examination, blood tests, endoscopic examination, and imaging tests (either abdominopelvic computed tomography or ultrasonogram) at least annually for the first 5 years [16]. For the next 5 years, patients will undergo endoscopic examination biannually (Fig 1).The results of HPE will be evaluated at the study endpoint using the RUT and histologic evaluation with Giemsa staining or IHC. H. pylori infection status will be considered negative only if both tests yield negative results [18].

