### Statistical analysis

#### General considerations.

The full details of the statistical analyses will be described in the Statistical Analysis Plan (SAP), which will be finalised prior to code breaking. Analyses will be performed using SAS software (SAS Institute, Inc., Cary, North Carolina, USA); The version used will be specified in the SAP. Categorical data will be summarised by the number and percentage of subjects in each category. Continuous variables will be summarised by descriptive statistics, including the number of observations, mean, standard deviation, median, minimum, and maximum.

We will use the Kaplan-Meier method to calculate the cumulative incidence of adenoma, adenocarcinoma, and hyperplastic polyps, as well as overall survival. These will be compared between the two treatment groups using the log-rank test. The HRs, with 95% CIs, will be estimated using a Cox proportional hazards model. The improvement rate of precancerous lesion and the eradication rate of HP will be compared between treatment groups using the Chi-square test or Fisher’s exact test.

Unless otherwise stated, all efficacy analyses (except for the primary endpoint) will be conducted with a two-sided test at a significance level of α = 0.05.

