#### FAS.

The FAS will include all randomized patients, which will constitute the intention-to-treat population. The FAS will be based on the treatment allocated (as randomized). All efficacy endpoints will be analysed using the FAS.

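### Infection is diagnosed at entry by any of three tests but cleared at the end by two, so patients positive only on the breath test can count as eradicated without any change in infection

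*Protocol article*

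**What the plan says.** **Entry.** Under Study protocol (baseline evaluation), three tests are done before surgery: urea breath test, RUT, and histology with Giemsa or IHC. The rule is: "HP infection will be diagnosed when any of the three studies showed positive results". The inclusion criteria require this diagnosis.

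**End of study.** Under Follow-up strategy: "The results of HPE will be evaluated at the study endpoint using the RUT and histologic evaluation with Giemsa staining or IHC". Status is negative only when both of these tests are negative. The breath test is not mentioned again. A literature reference is given for the rule, but no reason for leaving out the breath test.

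**Use.** Under Statistical analysis, General considerations: "the eradication rate of HP will be compared between treatment groups using the Chi-square test" or Fisher's exact test. That sentence names no denominator. The FAS section, which covers all randomised patients, says: "All efficacy endpoints will be analysed using the FAS".

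**The concern.** The definition of infected at entry is wider than the definition of infected at the end. A patient with a positive breath test, a negative RUT and negative histology is infected under the first rule. The same biopsy results at the end make that patient negative under the second. The move from infected to negative then comes from the change of tests.

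The end-of-study assessment is the only post-treatment measurement of infection that the article describes. It is what will show whether the regimen worked and whether placebo patients stayed infected. The Introduction reports spontaneous remission of HP in the remnant stomach after surgery. Breath-test-only entrants on placebo would look the same as such remission, so a measurement artefact could be read as biology. A smaller apparent contrast in infection would also make a null primary result harder to interpret.

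**Working it through.** The article gives no expected eradication rate and no share of breath-test-only entrants, so there is no planned figure to reproduce. The check has two parts: the logic of the two rules, then an illustration under stated assumptions.

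**Step 1. The two rules side by side**

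| Breath test | RUT | Histology | Entry rule | Two-test end rule, same biopsy results |
|---|---|---|---|---|
| any | + | any | infected | not negative |
| any | any | + | infected | not negative |
| + | − | − | **infected** | **negative** |
| − | − | − | not eligible | – |

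Only the third row changes category with no change in test results. Requiring both biopsy tests to be negative is strict within those two tests, but it cannot catch this patient. Nothing in the article limits the eradication comparison to biopsy-positive entrants or brings the breath test back.

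**Step 2. Effect on the rates**

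Inputs:
- u = share of randomised patients positive on the breath test alone. Not given; taken as 1% to 15%.
- True negativity at the end: 80% active, 10% placebo. Not given; assumed, and taken to be the same in breath-test-only and other patients.
- q = share of breath-test-only patients whose RUT and histology are both negative at the end. Set to 1, the largest possible value.
- 492 patients per arm (Abstract, Methods), all in the denominator (assumed).

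Formulas:
- Observed rate = (1 − u) × true rate + u × q.
- With q equal in both arms, contrast = (1 − u) × (80 − 10) = 70 × (1 − u).
- If q is higher on active than on placebo, the contrast is larger. So 70 × (1 − u) is the lower limit as long as q on active is at least q on placebo.

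Example for u = 5%: active 0.95 × 80 + 5 = 81.0%; placebo 0.95 × 10 + 5 = 14.5%; contrast 66.5 points.

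| u | Breath-test-only patients per arm (492u) | Active, at most | Placebo, at most | Contrast, at least |
|---|---|---|---|---|
| 0% | 0 | 80.0% | 10.0% | 70.0 |
| 1% | 5 | 80.2% | 10.9% | 69.3 |
| 3% | 15 | 80.6% | 12.7% | 67.9 |
| 5% | 25 | 81.0% | 14.5% | 66.5 |
| 10% | 49 | 82.0% | 19.0% | 63.0 |
| 15% | 74 | 83.0% | 23.5% | 59.5 |

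**Step 3. How large might u be?**

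If the three tests were independent with the same sensitivity s, the breath-test-only share of infected entrants would be s(1 − s)² / [1 − (1 − s)³]. This gives 0.032/0.992 = 3.2% at s = 80%, 0.9% at 90% and 0.2% at 95%. RUT and histology both depend on biopsy sampling, so their misses may be correlated, which would raise u. Neither assumption can be tested from the article, so the low rows deserve as much weight as the high ones.

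**Step 4. What does not depend on HP status**

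The primary endpoint is pathologically confirmed adenoma or adenocarcinoma. The FAS is all randomised patients. The per-protocol set turns on eligibility, treatment according to protocol and compliance of at least 75%. The 66 events and 984 patients come from neoplasm incidence. None of these uses end-of-study HP status.

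**The case against.** The strongest reply is that this is a detail of a supportive comparison. The eradication rate is not a listed primary or secondary endpoint. It appears in one sentence with a test and no denominator, and the article leaves further populations and full analysis details to an SAP that is not shown. This stands in part: the all-randomised denominator is a reading, because the FAS sentence speaks of efficacy endpoints and the eradication rate is not listed as one. But the two test sets are both fixed in the article and differ, so the mismatch is not a gap left to the SAP.

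A reader might infer several stronger things that the article does not support:
- **That breath-test-only entrants will always be scored as eradicated.** They are only if both biopsy tests stay negative; an infection missed once may be found later.
- **That they already meet the negative definition at randomisation.** The entry tests are done before surgery on the intact stomach. Enrolment is 3–4 weeks after surgery, and no RUT or histology of the remnant is described at that time.
- **That the mismatch favours one arm.** It applies to both blinded arms, dilutes the contrast and creates no false difference. Even at u = 15%, 83.0% against 23.5% with 492 per arm is unmistakable.

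Some breath-test-only results may also be false positives at entry. The end-of-study negative status would then be correct, but counting the patient as eradicated would still be wrong. Finally, whether leaving out the breath test is justified in a remnant stomach may be argued in the cited reference, which cannot be judged here. Such a justification would not align the two definitions.

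**Conclusion.** The point holds, at minor severity. The article states an entry rule and an end-of-study rule that do not match, and uses the second to compare eradication between arms. A breath-test-only entrant can be counted as eradicated in either arm with no change in infection, if RUT and histology remain negative.

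The size is unknown because u is not given. If all randomised patients are the denominator, the loss of contrast is at most 0.7 points at u = 1% and 10.5 points at u = 15% (70 − 69.3 and 70 − 59.5). These figures rest on the assumed 80% and 10% negativity and on q on active being no lower than on placebo. The practical risk is misreading placebo clearance. It would be wrong to infer any threat to the primary result's validity, since neither the primary endpoint nor its analysis sets, event count or sample size depend on HP status.

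**What to change.** Add one sentence to the eradication-rate analysis, in the protocol or in the SAP before code breaking: the rate is computed among randomised patients who were RUT-positive, histology-positive or both at baseline, so that the same two tests define infection at both times. Show breath-test-only entrants by arm on a separate line. Keep all randomised patients in the primary neoplasm analysis.

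The cost is small. The baseline results are already planned, and no test or visit is added. Selecting on a characteristic measured before randomisation keeps the comparison randomised. This supportive comparison loses the breath-test-only patients, probably few.

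One limitation remains and should be acknowledged when placebo clearance is interpreted: baseline biopsies come from the intact stomach and later ones from the remnant. Resection or postoperative change can turn a biopsy-positive patient negative, and this fix does not remove that.

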## Outcome measurements

### Primary endpoint

#### Incidence of adenoma and adenocarcinoma occurrence.

The incidence of adenoma or adenocarcinoma will be evaluated via endoscopy and confirmed by pathologically examining the corresponding lesion. Adenomas included in the analysis will encompass both low-grade and high-grade dysplasia. Once the development of adenoma or adenocarcinoma is identified, the investigators will be required to report the occurrence of the disease by recording this information in the eCRF without delay.

### Secondary endpoints

#### Overall survival.

All deaths of the enrolled patients during the trial will be reported to evaluate overall survival.

#### Improvement rate of precancerous lesions.

Biopsy specimens will be obtained from three sites, namely, the fundus and greater curvature of the body in the remnant stomach and the anastomosis site, to assess gastric glandular atrophy and intestinal metaplasia. These parameters will be evaluated according to the updated Sydney system and compared with the scores assessed before surgery.

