## Discussion

This double-blinded randomized clinical trial aims to evaluate the effectiveness of HPE in remnant stomach neoplasms after curative gastrectomy. The significance of the current study is described as follows.

First, a pivotal consideration in our research is the deliberate choice of adenoma and adenocarcinoma incidence in the remnant stomach as our primary outcomes. Thus, the effectiveness of HPE in terms of lesions requiring endoscopic or surgical intervention can be directly evaluated as a primary endpoint. Previous RCTs analysed the overall survival or changes in atrophy and metaplasia as primary outcomes; as such, deriving definitive conclusions about the actual impact of HPE on neoplasms in the remnant stomach is challenging [7,9]. With the release of our study results, we will provide critical insights into this matter.

Second, a 10-year long-term follow-up study post randomization will be implemented; thus, the prolonged effects of HPE will be assessed. Tumors that arise in the remnant stomach after curative gastrectomy for gastric cancer treatment require a minimum of approximately 7 years to develop [20–24]. Thus, extended tracking is necessary to investigate remnant stomach neoplasms.

Third, we aim to optimise the randomization process by incorporating the reconstruction method as a stratification factor. This strategic approach is designed to effectively control confounding variables, promote similarity in baseline characteristics, and improve the statistical power of our analysis. Previous research reported variations in the occurrence of remnant gastric cancer associated with different reconstruction methods [19,25–27]. A previous report suggested a higher risk of remnant gastric cancer in patients who underwent proximal gastrectomy, preserving the distal stomach [28]. Therefore, we will include patients who underwent proximal gastrectomy in our protocol. This inclusion is based on our expectation that proximal gastrectomy is associated with a relatively higher likelihood of occurrence of remnant gastric cancer. By incorporating these considerations, our study aims to contribute valuable insights into the reconstruction methods and their implications for remnant gastric cancer risk.

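### Biopsy sites for the atrophy/metaplasia improvement rate differ before and after surgery, and the single follow-up list does not fit proximal gastrectomy

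*Protocol article*

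**What the plan says.** All places are in the protocol article.

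- **Baseline** (Study protocol, baseline evaluation): atrophy and intestinal metaplasia "will be evaluated in biopsy specimens obtained from the gastric antrum, body, and fundus by using the updated Sydney system".
- **Follow-up** (Secondary endpoints, Improvement rate of precancerous lesions): three sites, "namely, the fundus and greater curvature of the body in the remnant stomach and the anastomosis site". The results are "compared with the scores assessed before surgery". One list is given for all patients, with no statement of which follow-up site is set against which baseline site.
- **Operations enrolled** (Inclusion criteria): patients "subjected to distal gastrectomy for cancer located in the lower half of the stomach (pylorus, antrum, and lower body") and patients "subjected to proximal gastrectomy for cancer located in the upper half of the stomach (fundus, cardia, upper body, and mid body"). Proximal gastrectomy is a separate randomisation level, "proximal gastrectomy with double tract reconstruction". The Discussion describes this group as "patients who underwent proximal gastrectomy, preserving the distal stomach".
- **Analysis** (Statistical analysis): the improvement rate is compared between arms by chi-square or Fisher's exact test, two-sided 0.05.

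**The concern.** A change from baseline is meaningful only if the same mucosa is scored both times. Here the two site lists differ, and the operation decides which sites survive. A score can therefore change because the biopsy came from a different part of the stomach, in either arm and with no healing or progression.

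The proximal-gastrectomy stratum is affected most. A listed site no longer exists, and a site that does exist and has a baseline score is left out. The Discussion says these patients were included because their risk of remnant cancer is expected to be higher. At stake are the readability of the improvement rate and the sensitivity of its between-arm test.

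**Working it through.** No stated figure needs reproducing. The main check sets the site lists against the operations.

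**Step 1. Site check.** That the antrum is removed in distal gastrectomy and the fundus in proximal gastrectomy follows from the operations and the tumour locations in the inclusion criteria; the article does not spell out the resection extent.

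| Site | Baseline score | Follow-up biopsy listed | After distal gastrectomy | After proximal gastrectomy |
|---|---|---|---|---|
| Fundus | yes | yes | matched by name | removed; biopsy cannot be taken |
| Body | yes (location not given) | yes (greater curvature) | matched by name | matched only if the baseline biopsy came from the retained part |
| Antrum | yes | no | removed | retained, but not sampled |
| Anastomosis | no | yes | no baseline | no baseline |

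Matched follow-up sites: 2 of 3 after distal gastrectomy, at most 1 of 3 after proximal gastrectomy. The body needs care in both groups. Upper-body and mid-body cancers lead to proximal gastrectomy and lower-body cancers to distal gastrectomy, so a baseline body biopsy may lie in the resected part.

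**Step 2. Number of patients without a fundus site.** The share having proximal gastrectomy is not given. Assuming 2% to 20%: 984 × 0.02 ≈ 20 to 984 × 0.20 ≈ 197 patients.

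**Step 3. Illustration of dilution.** The inputs from the article are 984 randomised, 10% dropout, 1:1 allocation and two-sided 0.05, so 984 × 0.9 / 2 ≈ 443 per arm. Everything else is assumed:

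- Pre-operative grade ≥1 in 60% at the antrum and in 30% of proximal-side mucosa.
- The anastomosis is set against the antral score and resembles proximal-side mucosa.
- A patient counts as improved if any site improves.
- The artefact applies to every patient, independently of true improvement.

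Spurious improvement with no true change, a:
- fully nested: 0.60 − 0.30 = 0.30
- independent: 0.60 × (1 − 0.30) = 0.42

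Observed rate = 1 − (1 − a)(1 − p), where p is the true site-matched improvement. Power is from the normal approximation for two proportions (pooled variance under the null), 443 per arm.

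| True improvement | a | Observed rates | Difference | Power |
|---|---|---|---|---|
| 20% vs 10% | 0 (site-matched) | 20.0% vs 10.0% | 10.0 points | 99% |
| 20% vs 10% | 0.30 | 44.0% vs 37.0% | 7.0 points | 57% |
| 20% vs 10% | 0.42 | 53.6% vs 47.8% | 5.8 points | 41% |
| 30% vs 15% | 0.30 | 51.0% vs 40.5% | 10.5 points | 88% |
| 30% vs 15% | 0.42 | 59.4% vs 50.7% | 8.7 points | 74% |
| 40% vs 20% | 0.30 | 58.0% vs 44.0% | 14.0 points | 99% |
| 40% vs 20% | 0.42 | 65.2% vs 53.6% | 11.6 points | 94% |

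Under this rule the true difference is multiplied by (1 − a). If p is equal in the two arms, the observed rates are also equal, so no false difference is expected.

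**The case against.** The strongest reply is that the article gives no pairing, no rule for combining sites and no definition of a patient who has improved. It refers full statistical details to a SAP that is not shown. If the SAP pairs fundus with fundus and body with body, the distal-gastrectomy artefact from antrum and anastomosis disappears and that power loss is zero. This stands: any statement of size is conditional.

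It does not remove the point. The article itself fixes the collection sites, and no analysis rule can supply antral follow-up tissue that was never taken or a biopsy from a resected fundus.

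Three stronger readings are tempting, and the documents do not support them:

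- **That the plan scores the anastomosis against the antrum.** A reader might infer this because each list has three entries and these two are left over. It is not stated.
- **That the improvement rate cannot be interpreted at all.** Two of the three sites match by name after distal gastrectomy. The direction of any artefact is also open: the Introduction describes alkaline reflux after surgery, so anastomotic scores need not be lower than antral ones.
- **That the arm comparison is biased.** Allocation is randomised, double-blind and stratified by reconstruction, with proximal gastrectomy as its own level. A site shift is expected to fall equally on both arms.

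The power figures also depend heavily on the assumed effect, as the 40% vs 20% rows show.

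**Conclusion.** The concern holds for what the article fixes. The baseline and follow-up sites do not match, and the single follow-up list is unsuitable for proximal gastrectomy, where one listed site is absent and a retained, scored site is skipped. This needs only the text and the nature of the two operations.

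The consequence is conditional. If unmatched sites enter the improvement rate, the absolute rate becomes hard to interpret and the arm difference can be diluted. The loss of power runs from none, with site-matched scoring, to large under the assumed any-site rule (99% down to about 57% or 41% for 20% vs 10%). No false positive difference is expected. The number of proximal-gastrectomy patients is unknown.

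The endpoint is secondary; the primary endpoint, its 66 events and the 984 patients are untouched. Severity: should fix, for this endpoint only.

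**What to change.** In the section on the improvement rate of precancerous lesions, replace the single list with a site map by operation:

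- **Distal gastrectomy:** fundus and body, each compared with its own baseline score.
- **Proximal gastrectomy:** antrum and retained body. The antral biopsy takes the place of the fundus biopsy, so the number of biopsies is unchanged.
- **Both:** define improvement only on sites present and scored before and after surgery. Record the body location at both times (greater curvature, and within the retained part), and count a body pair only where the baseline site was retained.
- **Anastomosis:** report only as a between-arm comparison of follow-up scores, not as change from baseline.

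The cost is a paragraph of protocol and SAP wording and a site field on the eCRF. The downside is that the anastomosis leaves the improvement rate and some patients contribute fewer matched sites. Recruitment runs to the end of 2028 and follow-up to the end of 2038, so most follow-up sampling can still be corrected. Antral tissue not taken at a past visit cannot be recovered.
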